### Statistical analysis

2.15

The following four datasets will be used for the analysis [1]: the data of all volunteers who completed the follow-up and [2] the data of three subgroups divided according to compliance (≥80%, 60–80%, and <60%), which will be analysed to validate the robustness of the analysis results. The following analysis methods will be used to analyse each dataset.

First, to analyse the inter-group differences in each outcome measure, Z test (as the sample size is quite more than 10, using Z test instead of Wilcoxon signed-rank sum test) will be used for the outcome measures, including the diarrhoea severity score, weekly mean frequency of defecation, weekly mean stool appearance score, weekly mean stool urgency score, and emotional state score, at each observation point. In the analyses, the *P*-value indicating statistical significance will be set at 0.05. More detailed information about how to analyse and present inter-group differences is clearly provided in Table 2.

**Table 2 tbl2:** The format to analyse and present the inter-group differences between probiotic and placebo groups at each observation point.

Groups	P5	P25	Median	P75	P95	Z value	*P*
*L. plantarum* p9							
Placebo							

Note: The data applied here includes the diarrhoea severity score, weekly mean frequency of defecation, weekly mean stool appearance score, weekly mean stool urgency score, and emotional state score; P5, P25, P75, P95 means the 5th, 25th, 75th, 95th percentile, respectively; Z = |T-n1*(N+1)/2–0.5|/SQRT [n1*n2(N+1)/12], n1 refers to the smaller sample size between the two compared groups, while n2 refers to the sample size of the other group; N = n1+n2; T is calculated using method of Wilcoxon signed-rank sum test.

Then, to identify the intra-group changing trends with the consecutive phases, namely, pre-, during and post-probiotic administrating, the *Kruskal-Wallis* rank sum test will be used for multiple comparisons of the diarrhoea severity score, weekly mean frequency of defecation, weekly mean stool appearance score, weekly mean stool urgency score, and emotional state score for each group, i.e., probiotic group or placebo group. In the analyses, the *P*-value indicating statistical significance will be adjusted to be 0.05/[k(k-1)/2], where k is the number of sample groups in the comparison. More detailed information about how to analyse and present inter-group differences is clearly provided in Table 3.

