**Table 3 tbl3:** The format to analyse and present the intra-group differences among the four observation points in a probiotic or placebo group.

Groups	P5	P25	Median	P75	P95	H value	*P*
Day 0							
Day 14							
Day 28							
Day 42							

Note: The data here includes the diarrhoea severity score, weekly mean frequency of defecation, weekly mean stool appearance score, weekly mean stool urgency score, and emotional state score; P5, P25, P75, P95 means the 5th, 25th, 75th, 95th percentile, respectively; H is calculated using method of *Kruskal-Wallis* rank sum test.

In addition, the statistical analyses of metagenomics and metabolomics will be performed using the R software (v.4.0.2) and Adobe Illustrator. PCA and PLS-DA analysis will be performed and visualized using the R package vegan, ggplot and ggpubr, and the adonis *P*-value will be generated based on 999 permutations. *t*-test, *Wilcoxon* test and *Kruskal-Wallis* test will be used to evaluate differences in various variables between and within groups; *P* values will be corrected for multiple testing using the Benjamini-Hochberg procedure. Meanwhile, Pearson and spearman correlations will be used to analyse the correlations between different indicators in clinical, metagenomics and metabolomics.

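### Section 2.15 judges one within-group omnibus test over four days at a pairwise Bonferroni level, 0.0083 instead of 0.05

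*Protocol article*

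**What the plan says.** Section 2.15 (Statistical analysis) treats the within-group analysis separately from the between-group one. For each arm, the Kruskal-Wallis "rank sum test will be used for multiple comparisons of the diarrhoea severity score" and for the four other clinical outcomes. The significance level for these analyses "will be adjusted to be 0.05/[k(k-1)/2], where k is the number of sample groups in the comparison".

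The text refers to Table 3 for the detail. Its caption reads "The format to analyse and present the intra-group differences among the four observation points in a probiotic or placebo group". The table has one row for each of days 0, 14, 28 and 42, percentile columns, one H column and one P column. Its note says only that "H is calculated using method of *Kruskal-Wallis* rank sum test". Neither the text nor the table names a pairwise test or leaves room for a pairwise P value.

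For the between-group comparisons the P "value indicating statistical significance will be set at 0.05", with no division.

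**The concern.** The quantity k(k-1)/2 is the number of pairs that can be formed from k samples. Dividing 0.05 by it gives the Bonferroni level for each of those pairs. An omnibus test over k samples is one test of one null hypothesis, and it needs no such division.

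The plan attaches the pairwise level to the omnibus test. The only within-group P value it produces is the one beside H, and the only level it gives for that P value is the divided one. An analyst who follows the text would report no change over time for any within-arm P between 0.0083 and 0.05, although 0.05 is the proper level for that single test.

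The rule covers five outcomes in two arms, and section 2.15 applies its methods to each of four datasets: 5 × 2 × 4 = 40 within-arm tests. The Abstract lists within-group differences among the things to be identified, and the Discussion relies on them, beside the between-group results, to present the effect of the product.

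**Working it through.** **Inputs**

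- Level: 0.05/[k(k-1)/2], section 2.15.
- k: four observation days, Table 3.
- Test: Kruskal-Wallis H, section 2.15 and the note to Table 3.
- Degrees of freedom for H: k - 1 = 3.

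**Step 1. The plan's level.** The article prints only the formula. With k = 4 there are 4 × 3/2 = 6 pairs, and 0.05/6 = 0.00833.

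**Step 2. That level applied to the single H test.** The chi-square quantiles on 3 df are:

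| Level | Critical H |
|---|---|
| 0.05 | 7.81 |
| 0.00833 | 11.74 |

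The level is stricter by 0.05/0.00833 = 6.

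**Step 3. Power cost for a valid 3-df test.** A non-central chi-square on 3 df with non-centrality of about 10.9 exceeds 7.81 with probability 0.80. The same distribution exceeds 11.74 with probability 0.57. So 80% power at 0.05 becomes about 57%. This assumes that the chi-square reference is valid for the statistic used. A Friedman test over four days also has 3 df, so changing to a repeated-measures omnibus test would leave this mismatch in place.

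**Step 4. The same level applied to six pairs with k = 4.** The levels sum to 6 × 0.00833 = 0.05. If the six tests were independent, the chance of any false difference would be 1 - (1 - 0.00833)^6 = 0.049. On this use the formula is ordinary Bonferroni and holds 5%.

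**Step 5. What the article shows.** Step 4 requires six pairwise P values per outcome and arm. Table 3 has one P beside one H, which is the situation of step 2.

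**Step 6. Whether k is fixed.** Table 3 has four days. The sentence in section 2.15 speaks of consecutive phases, "namely, pre-, during and post-probiotic administrating", which are three. With k = 3 the formula gives 0.05/3 = 0.0167. Table 3 makes four the natural value, but the article does not say so.

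**The case against.** The strongest reply is that the authors mean pairwise comparisons. The text says the test is used for multiple comparisons, the formula is the standard pairwise Bonferroni level, and four observation points give 0.0083 per pair, which holds the family error at 5%. On that reading the level is right, and what is missing is the name of the pairwise test, which an article may leave to the full protocol. Table 3 is only a blank layout. This stands in part: the formula is sound for six pairs, and pairwise comparisons are probably what was meant. It does not remove the point, because the article does state a test, a level and an output format, and the three do not fit together. The valid reading depends on tests and P values that are not written down.

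A reader might go further and infer that the rule gives no correction when days are compared in pairs, because k would then be 2 and the level 0.05/1 = 0.05. The documents do not support that. An adjustment formula that always returned 0.05 would never adjust, and Table 3 points to k = 4.

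Nor can one conclude that no reading holds the error at 5%. The omnibus reading errs on the strict side, and the pairwise reading with k = 4 holds 5%.

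A false-positive rate of about 0.21 for six uncorrected pairs does not describe this plan either. It depends on the k = 2 reading and on paired tests or independent samples. The planned rank sum test was simulated on all six pairs at 0.05 each, under the null, with 100 volunteers and 4000 runs. It gave at least one false difference in 0.198 of runs at a within-person correlation of 0, 0.099 at 0.3, 0.038 at 0.5 and 0.003 at 0.7. The correlations are assumed, as the article gives none.

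The stakes are also limited, and that part of the objection stands in full: only within-arm analyses are touched.

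**Conclusion.** The point holds as a mismatch between the stated level, the only named test and the output table. Followed as written with k = 4, the plan judges one omnibus test at 0.0083, six times too strict, with a critical H of 11.74 against 7.81. The fall in power from 80% to about 57% applies to a valid 3-df test and shows the size of the loss; it is not a forecast for this trial. Using Kruskal-Wallis on repeated measurements from the same volunteers is a separate issue, and it alters the test's true error rate whatever level is chosen.

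The consequence is missed or under-reported change over time within arms, not inflated false claims. The between-group comparisons, including the primary outcome, are tested at 0.05 and do not change, so the efficacy conclusion does not depend on this. The correction is worth making because the rule is stated, governs many reported P values, and is easily put right.

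**What to change.** Rewrite the sentence on the within-group level in section 2.15 as two steps:

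1. Judge the omnibus test over the four observation days at 0.05.
2. Only if it is significant, compare days in pairs with a named paired test (for example the Wilcoxon signed-rank test), each at 0.05/6 = 0.0083, or with Holm's procedure over the six pairs.

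State that k = 4 is the number of observation days, and add the pairwise P values to Table 3. This controls error within one outcome in one arm; it makes no claim across outcomes, arms or datasets.

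The cost is a short rewrite of one sentence and extra columns in one table. No new data are needed, and the sample size and between-group analysis stay as they are.

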## Discussion

3

Chronic diarrhoea can disturb the patient's quality of life, work performance and wellbeing, increase patient's expenses [10], and leads to economical loss because of work-loss [11]. Probiotics may offer a way for the problems [[12], [13], [14], [15], [16], [17],^31^]. However, clinical trials pin-pointing the effectiveness of probiotics for chronic diarrhoea are currently limited. In this specific context, we design the study protocol. This is the first study protocol designed to assess whether the probiotic can improve the symptoms of patients with chronic diarrhoea (previous studies using nonhuman primates or not only focus on chronic diarrhoea).

Some special steps are taken to guarantee the eligibility of volunteers, the feasibility of study, and interpretability of results, including completing diary online daily (for recording the times, appearance and urgency feeling of defecation), face-to-face consultation with the clinical specialist (confirming the realness of information provided online by volunteers), and stool test (excluding intestinal organic lesion) in the 14 days screening period. The study intervention, *L. plantarum* p9, belongs to *Lactobacillus* species, which is one of the most studied probiotics [41,42] and reported to be beneficial in reducing the risk of developing *Clostridium difficile*-associated diarrhoea [17,43] and the overall risk of diarrhoea lasting four or more days by 59% and the average duration thereof by 25 h [44].

Multidimensional outcomes are examined to produce a chain of evidence from causal improvements in metagenomic and metabolomic data to clinical symptoms and then to the emotional state. Chronic diarrhoea can disturb the patient's quality of life, work performance and wellbeing [10]; thereby, the relevant outcomes are chosen, including the diarrhoea severity score [33,34], weekly mean frequency of defecation, weekly mean stool appearance score [33,37], weekly mean stool urgency score [34], emotional state score [38] according to corresponding references [33,34,37,38]. The diarrhoea severity score is a comprehensive indicator calculated from weekly mean frequency of defecation, weekly mean stool appearance score, and weekly mean stool urgency score as described in “Primary outcome part”, so it is more reasonable to be the primary outcome than the left. Furthermore, both of inter- and intra-group differences will be analysed. In our opinion, the results of analysis are appropriate to present the effect of *L. plantarum* P9 on defecation and quality of life in individuals with chronic diarrhoea. Moreover, the study will try to explore the possible action modes of probiotics to improve chronic diarrhoea, from the aspects of gut microbiome and faecal metabolome. Gut microbiome has been found to be altered in chronic diarrhoea patients and may be a cause of chronic diarrhoea [12]. Probiotics are live organisms that when administered in adequate amounts confer health benefits to the host and improve the gut microbial balance [[13], [14], [15], [16], [17],^26^]. The detection of gut microbiome and faecal metabolome would provide an explanation for the efficacy of *L. plantarum* P9 on chronic diarrhoea. Thus, the set of multidimensional outcomes will form a chain of evidence.

A limitation is the way of follow up in this study (completing diary online daily), which may lead to bias about the effectiveness of probiotics. To overcome the limitation, a WeChat group is established for the cohort of volunteers, so the researcher can timely post messages via the WeChat group, keeping a good compliance; and an DMT is formed to promptly assess the study quality and safety. during the assessment, once an uncertainty about the data arises, the DMT can urge the data collectors to resolve it. The confounding factors are also prohibited. In such a way, the bias would be minimized as far as possible.

Collectively, the study protocol will provide high-quality evidence for the use of probiotics as a diarrhoea agent when it is strictly conducted out, providing evidence regarding whether and to what extent *L. plantarum* p9 can improve the defecation and well-being of individuals with chronic diarrhoea. If the study findings are as expected, *L. plantarum* p9, taken as probiotics, may become an optimal nonmedical intervention option for patients with chronic diarrhoea.

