**Method:**

A randomized, double-blind, placebo-controlled clinical trial is designed to pinpoint the efficiency and possible action modes of probiotics for chronic diarrhoea. 200 eligible volunteers with chronic diarrhoea are randomly assigned to a probiotic group (orally taking *Lactobacillus plantarum* p9 probiotics powder) or a placebo group. Except an independent project administrator who will be responsible for unblinding, the other researchers are blinded. Primary outcome is diarrhoea severity score, and secondary outcomes include weekly mean frequency of defecation, weekly mean stool appearance score, weekly mean stool urgency score, emotional state score, gut microbiome, and faecal metabolome. Each outcome measure will be assessed at the timepoints of pre-administration (day 0), administration (day 14 and/or 28), and post-administration (day 42) to identity inter- and intra-groups differences. Adverse events will be recorded to evaluate the safety of *L. plantarum* p9.

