	Gut microbiome		**✓**		**✓**	**✓**
	Faecal metabolome		**✓**		**✓**	**✓**
Safety measures	Adverse events (AEs)			**✓**	**✓**	**✓**
	Serious adverse events (SAEs)			**✓**	**✓**	**✓**
Verification of compliance with the intervention					**✓**	
Special situations related to defecation (e.g., concomitant medications)			**✓**	**✓**	**✓**	**✓**

Note: The outcome measures, weekly mean frequency of defecation, weekly mean stool appearance score and weekly mean stool urgency score are calculated from the defecation diary. The defecation diary completed from day −14 to −1 will be used for volunteer selection and baseline data. The detection of gut microbiome will be conducted within 2 months after the end of follow-ups, and the detection of faecal metabolome will be implemented within 2 months when data analysis finds that the probiotics present significant effect on gut microbiome.

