### Primary outcome

2.8

The primary outcome is the diarrhoea severity score, which is set as to the gastrointestinal symptom rating scale (GSRS) [[33], [34], [35], [36]]. The outcome measure is equal to the sum of mean defecation frequency score per day, mean stool consistency score per time, and mean stool urgency score per time within the past 7 days (see Appendix 2). The diarrhoea severity score will be assessed on days 0 (baseline), 14, 28, and 42. A higher score indicates more severe diarrhoea, Table 1. The details of calculation are as follows.

A defecation diary developed with reference to the literatures [33,34,37] will be completed daily online by the volunteers (Appendix 2). Based on the diary, the mean defecation frequency score per day, mean stool consistency score per time, and mean stool urgency score per time will be obtained. The defecation frequency score is ranked as: 0-point, one to two a day; 1-point, three to four times a day; 2-point, five to six times a day; 3-point, seven times a day or more frequently. The mean defecation frequency score per day is equal to “total defecation frequency score within the past 7 days/7”. The stool appearance score refers to Bristol stool type (Appendix 1) and must be recorded for each defecation: types 4–7 correspond to 0–3 points, respectively. The mean stool consistency score per time is equal to “total stool consistency scores within the past 7 days/total times”. The stool urgency score must be also recorded for each defecation: 0-point, no urgency; 1-point, a little urgency; 2-point, sudden need to have a defecation that must be addressed immediately; or 3-point, incontinence resulting in uncontrolled defecation and may stain pants. The mean stool urgency score per time is equal to “total stool urgency score within the past 7 days/total times”.

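### The Discussion claims a causal chain from microbiome and metabolome to symptoms to mood, but the sampling schedule and arm-blind correlations support only association between these levels

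*Protocol article*

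**What the plan says.** Section 3 (Discussion) sets the aim: "Multidimensional outcomes are examined to produce a chain of evidence from causal improvements in metagenomic and metabolomic data to clinical symptoms", continuing to emotional state. The same paragraph closes without condition: "Thus, the set of multidimensional outcomes will form a chain of evidence". Between these two statements stands a softer one: "the study will try to explore the possible action modes of probiotics".

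On timing, section 2.8 says: "The diarrhoea severity score will be assessed on days 0 (baseline), 14, 28, and 42". Its three components are averaged over the week before each visit, for example "mean stool urgency score per time within the past 7 days". Section 2.9 and Table 1 put DASS-21 on the same four days. Table 1 and section 2.14 put the stool samples for microbiome and metabolome on days 0, 28 and 42. Dosing runs from day 0 to day 28 (section 2.6).

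On analysis, section 2.15 connects the levels in one sentence: "Pearson and spearman correlations will be used to analyse the correlations between different indicators in clinical, metagenomics and metabolomics". Section 2.9 adds only a correlation analysis between microbiota and metabolites.

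On the metabolome, the note to Table 1 says: "the detection of faecal metabolome will be implemented within 2 months when data analysis finds that the probiotics present significant effect on gut microbiome". Section 2.14 gives the matching rule that the assay is not done if there is no microbiome effect. The abstract and the text of section 2.9 list the metabolome among the secondary outcomes without this condition.

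**The concern.** Randomisation lets the trial say that the product caused a change in the microbiome, in symptoms or in mood, each taken separately. It does not by itself show that one of these changes led to another. For that, one would want the supposed cause observed ahead of the supposed effect, or at least an analysis that separates an omics-symptom link from the fact that both may move with treatment. The article describes neither, yet it announces a causal chain.

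At stake is the mechanistic conclusion. A significant correlation between a taxon and the diarrhoea score could be presented as the way the product works when it shows only that both differ between arms. The risk is concrete here because each active pack contains 100 billion CFU of the organism itself (section 2.6), so a difference between arms in that organism in stool is likely whatever happens to symptoms.

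**Working it through.** **1. Schedule, side by side** (Table 1; sections 2.8, 2.9 and 2.14)

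| Level | Day 0 | Day 14 | Day 28 | Day 42 |
|---|---|---|---|---|
| Diarrhoea severity score | yes | yes | yes | yes |
| DASS-21 | yes | yes | yes | yes |
| Microbiome, metabolome (if assayed) | yes | no | yes | yes |

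- First post-baseline symptom and mood reading: day 14. First post-baseline omics reading: day 28, so 28 − 14 = 14 days later.
- On day 28 the symptom score covers the preceding 7 days, so the stool sample falls at the end of the symptom window, not before it.
- Day 28 omics do precede the day 42 symptom window and DASS-21. Dosing has stopped in between, so this lag describes withdrawal of the product, not its onset.
- Symptoms and mood share all four visits, so no scheduled mood reading follows its matching symptom reading at a later visit.

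**2. What a correlation over both arms can show**

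Assumptions, none of them in the article: two equal arms, within-arm SD 1 for both variables, within-arm correlation 0, and differences between arms of d1 (taxon) and d2 (symptoms) in absolute size. Completers: 200 × 0.80 = 160, from the planned total and the 20% drop-out allowance in section 2.13.

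With half the sample in each arm, the pooled covariance is d1·d2/4 and each pooled variance is 1 + d²/4, so

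r = (d1·d2/4) / √[(1 + d1²/4)(1 + d2²/4)].

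Power at two-sided 0.05 is approximately Φ(atanh(r)·√157 − 1.96), with 157 = 160 − 3.

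| d1 | d2 | r | Power |
|---|---|---|---|
| 2 | 0.5 | 0.25/√(2 × 1.0625) = 0.17 | 58% |
| 2 | 1 | 0.50/√(2 × 1.25) = 0.32 | 98% |
| 1 | 0.5 | 0.125/√(1.25 × 1.0625) = 0.11 | 28% |

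In the first row an observed r equal to the expected value has p = 0.03. In every row the correlation within either arm is zero. When the three cases were simulated with adjustment for arm, the significant share fell to about 5%, the nominal rate.

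**3. Direction remains open even after adjusting for arm**

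Three models with assumed coefficients were simulated (N = 200,000; A = arm, M = omics, S = symptoms, U = an unmeasured common cause, e = standard normal noise).

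| Model | Effect of A on S | Effect of A on M | Pooled r | Within-arm r |
|---|---|---|---|---|
| Omics lead: M = 0.5A + e, S = 0.8M + 0.8e | 0.40 | 0.50 | 0.72 | 0.8/√1.28 = 0.71 |
| Symptoms lead: S = 0.4A + e, M = S + 0.8e | 0.40 | 0.40 | 0.79 | 1/√1.64 = 0.78 |
| Common cause: M = 0.5A + 0.88U + 0.5e, S = 0.4A + 0.88U + 0.5e | 0.41 | 0.51 | 0.77 | 0.7744/1.0244 = 0.76 |

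Comparisons between arms plus correlations look much the same in all three. Adjusting for arm removes the artefact in step 2, but it does not establish which level drives which.

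**The case against.** The strongest reply is that the article's mechanistic language is largely exploratory, that the full protocol or analysis plan may say how the correlations are computed, and that the primary outcome and the randomised comparison of each level are sound. Much of this stands. It limits the point to the mechanistic claim. It does not remove it, because the softer sentence sits between two that announce the chain without reservation, and no unseen analysis can supply a stool sample on or before day 14.

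Four stronger readings are tempting, and the article does not support them:

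- **That all levels are read at the same visits.** They are not: day 14 has symptoms and mood without omics.
- **That the supposed cause is never observed before the supposed effect.** Day 28 omics precede the day 42 readings. What is true is that no post-baseline sample precedes the first post-baseline symptom reading.
- **That the metabolome link can never be contradicted.** The condition is a microbiome effect, not a metabolome result. Once assayed, the metabolome may show nothing, and if it is not assayed the chain has already failed at the microbiome. The condition is also disclosed in the note to Table 1 and in section 2.14.
- **That the plan is to pool the arms.** Section 2.15 does not say so; it leaves the choice open.

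The 58% is also hypothetical. It depends on pooling, on assumed shifts and on an unadjusted 0.05. Section 2.15 applies Benjamini-Hochberg to the omics tests, and whether that covers the correlations is unclear. If it does, a single p of 0.03 among many taxa would be unlikely to survive.

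**Conclusion.** The point holds for the claim about links between levels. The Discussion promises causal links that the stated design cannot establish. The first on-treatment omics reading follows the first symptom and mood readings by two weeks, the one lag with omics first spans the end of dosing, symptoms and mood coincide at every visit, and the only linking analysis is correlation that does not mention arm.

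If the arms are pooled, treatment assignment alone can produce correlations of 0.11 to 0.32, significant in 28% to 98% of trials with 160 completers. These figures assume shifts of 1 to 2 SD in the taxon and 0.5 to 1 SD in symptoms, no within-arm correlation, and no multiplicity correction.

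The causal effect of treatment on each level separately remains estimable, and the primary comparison and sample size are unaffected. The matter deserves correction because a stated aim would otherwise be over-claimed and the remedy is nearly free.

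**What to change.** - **Section 2.15:** specify that correlations between clinical, microbiome and metabolome measures use change from day 0 and are computed within arm, or as partial correlations adjusted for arm.
- **Section 3:** reword the opening and closing chain statements so that links between levels are described as associational and hypothesis-generating. Keep causal wording for the randomised effect of treatment on each level.
- **Abstract and section 2.9:** state that the faecal metabolome is measured only if a microbiome effect is found, as the note to Table 1 and section 2.14 already say. This is for consistency; whether to call it secondary or exploratory is a matter of preference.

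The cost is a weaker mechanistic claim. No extra samples or visits are needed. The article reports 174 of 200 enrolled and schedules microbiome detection after follow-up ends, so on its own timetable the correlation analysis could be fixed before any omics results exist. These changes do not repair the timing; they bring the claim into line with what the schedule can support.
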